**Fig. 3 Fig3:**
[figure not shown]
Visual illustration of the core components of the Health Dialogue Intervention and the Opportunistic Screening. Created with BioRender.com

### Implementation strategies

The implementation strategies that will be used to support implementation of the two interventions are labeled according to the Expert Recommendations for Implementing Change compilation of implementation strategies [29].

#### Educational meetings and educational materials

Prior to the start of the trial, all healthcare professionals providing the HDI intervention will complete a formal education in lifestyle-focused health dialogues as per the Swedish prevention program (1 day) and healthy lifestyle behaviors (1–2 days). Additionally, those not previously trained in motivational interviewing will complete a 2-day education in the method. For healthcare professionals providing the OS intervention, a short educational meeting will be provided to all healthcare professionals. The meeting will describe the purpose of the screening, how to conduct the screening, and measures to take when risk factors are detected, which includes treatment according to the existing care programs and clinical practice guidelines (https://viss.nu/). Educational materials detailing how the interventions should be delivered will be developed and distributed to the healthcare professionals in both arms prior to the trial.

#### Ongoing consultation

In both arms, ongoing consultation will be provided on an as-needed basis to continuously support the healthcare professionals delivering the interventions and help them solve potential problems. The consultation will be provided either at the PCC or online by a member from the project team.

### Outcomes and measures

This trial will assess a wide range of outcomes which can be grouped according to the following domains: biological risk factors, lifestyle habits, process and implementation, unintended side effects, short-term health outcomes, and long-term health outcomes and resource use.

### Biological risk factors

Biological risk factors, used as surrogate outcomes for the target outcomes CVD and T2D, will be assessed at baseline and at 6 months and 12 months post intervention. These include systolic blood pressure (primary outcome), body mass index, fasting blood glucose, total cholesterol, high-density lipoprotein cholesterol, and low-density lipoprotein cholesterol. The main reason for using systolic blood pressure as a primary outcome rather than the target outcomes was practical, as the internal funding for the trial was limited to 2025, for which it would not have been possible to determine the effect of the intervention on the target outcomes (i.e., CVD and T2D incidence). Additionally, the use of surrogate endpoints was justified based on the large-scale evidence on their implications in CVD and T2D [1, 30, 31]. Blood pressure (mmHg) will be measured in a seated position using digital devices. Two measurements will be made with a one-minute rest in-between. The mean value of the two measurements will be recorded. Body weight will be measured using digital scales and height using stadiometers, after which the body mass index will be calculated as the weight in kilograms over the height in meters squared. Blood samples (mmol/l) will be drawn and analyzed according to routine practice at accredited laboratories associated with each of the participating PCCs. All participants are instructed to leave blood samples in a fasted (≥ 12 h) state.

### Lifestyle habits

Dietary habits, tobacco/nicotine use, alcohol consumption, and physical activity will be assessed at baseline and at 6 months and 12 months post intervention through self-report using questions recommended by the National Board of Health and Welfare [32]. The specific questions and response categories are outlined in Additional file 5.

### Short-term health outcomes

The HRQoL will be assessed at baseline and at 6 months and 12 months post intervention using the EQ-5D instrument [33]. The EQ-5D is a generic patient-reported outcome measure of HRQoL across five dimensions (mobility, self-care, usual activities, pain/discomfort, anxiety/depression), each with five response options. Using predetermined value sets, an index value can be derived from the responses in the five dimensions. In this study, a Swedish value set recommended by EuroQol will be used [34]. For generalizability of results, index values based on additional value sets will also be calculated, in line with updated guidelines at the time of conducting the study.

### Long-term health outcomes and resource use

To examine the effect on long-term health outcomes, cases of incident T2D and CVD (ischemic heart disease and stroke) and deaths due to T2D and CVD will be collected during 5 and 10 years of follow-up from regional and nationwide health registers, using International Classification of Diseases, 10th revision (ICD-10) codes E11 for T2D and I00-I99 for CVD. The registers that will be used are the National Patient Register, the National Cause of Death Register, the National Diabetes Register, and the Stockholm Regional Healthcare Data Warehouse. The National Patient Register includes data on all inpatient care in Sweden with 100% coverage since 1987, and since 2001, it also includes data on specialized outpatient care [35]. The Cause of Death Register covers data on all deaths in Sweden since 1952 [36]. Both of these registers are managed by the National Board of Health and Welfare. The National Diabetes Register was initiated in 1996, has 87% coverage, and includes data on patients with a diagnosis of diabetes, regardless of the care provider, thus including also primary data in contrast to the National Patient Register [37, 38]. This register is managed by Register Centre, Västra Götaland, Sweden. The Stockholm Regional Healthcare Data Warehouse (VAL) is a regional database including data on diagnoses and healthcare utilization from inpatient, specialized outpatient, and primary care for all people living in Stockholm Region since 1997 [39]. The coverage is complete since 2013 [37]. Additionally, information on prescribed medications for T2D and CVD (at baseline and during follow-up) will be collected from the Prescribed Drug Register using Anatomical Therapeutic Chemical codes A10, C02-C03, C07-C10. The Prescribed Drug Register is managed by the National Board of Health and Welfare and includes data on all prescribed medications that are collected at Swedish pharmacies since July 2005 [40]. Cost data will be collected from regional pricelists, the Cost Per Patient database, held at the Swedish Association of Local Authorities and Regions, and the national pricelist of reimbursed medications, held at the Dental and Pharmaceutical Benefits Agency.

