The intervention will be conducted according to the following procedure. First, ahead of the scheduled health dialogue, participants will be asked to fill out a health survey. For participants with language barriers, it will be possible to fill out the survey with the assistance from an interpreter in their native language in conjunction with the forthcoming health dialogue. The survey assesses various aspects of health status and lifestyle habits, including medical history, medications, general health, mental health, heredity, living situation, quality-of-life, alcohol consumption, dietary habits, tobacco and/or nicotine use, and physical activity. Second, participants will be instructed to leave blood samples no more than 7 days prior to the scheduled health dialogue, where cholesterol levels and glucose levels are measured. Finally, the participants will arrive at their PCC for the scheduled health dialogue. The appointment will begin with an assessment of body weight, height, waist-to-hip ratio, and blood pressure. These data will then be incorporated, together with the blood sampling results and the survey data, into a risk profile assessment tool providing a visual result of the participant’s risk profile, known as the “Health Curve.” The risk profile displays a gradient in CVD risk ranging from green (low risk), yellow, to red (high risk) [14, 28]. Finally, the healthcare professional will use motivational interviewing techniques to perform an individually oriented, lifestyle-focused health dialogue guided by the risk profile. In total, the appointment is scheduled to take about 75–90 min including preparation time, the health dialogue, and administration. The actual dialogue is expected to take about 60 min, and for participants in need of an interpreter, an additional 30 min is expected. Notwithstanding the personalized health dialogue, detected risk factors for T2D and CVD (e.g., hypertension) will also be managed in accordance with existing care programs and clinical practice guidelines (https://viss.nu/). There are no criteria for discontinuing the intervention. There is no concomitant care that is prohibited during the trial.

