### Process and implementation outcomes

Process and implementation outcomes will be assessed 6 months post intervention according to Proctor et al.’s taxonomy [41]. Adoption will be measured as the number of invited PCCs that agree to participate in the study. Healthcare professionals’ perceptions of how acceptable, appropriate, and feasible the interventions are to implement within the context of the PCCs will be assessed using the Acceptability of Intervention Measure, the Intervention Appropriateness Measure, and the Feasibility of Intervention Measure [42]. The measures consist of four items each and responses are reported on a 5-point Likert scale ranging from “completely disagree” to “completely agree.” Fidelity will be operationalized as adherence to the original intervention protocols and assessed using data from electronic medical records. For the HDI, we will report to what extent (proportion) all parameters of the screening have been assessed and whether the following health dialogue has been conducted, as based on documentation in the patients’ electronic medical records. For the OS, we will assess to what extent (proportion) all parameters of the screening have been assessed and to what extent that identification of an elevated risk factor has resulted in measures taken according to existing clinical practice guidelines. (For example, what proportion of participants who report daily smoking are given brief advice about smoking cessation and asked whether they want a referral to a qualified tobacco cessation advisor.) Penetration will be assessed in terms of the proportion (in both arms) of patients choosing to participate among those invited (attendance rate), and the reasons for declining participation among non-participants. We will also report (in both arms) the representativeness of participants as compared to the total eligible population based on socioeconomic characteristics. Participants data on sex, level of education, occupation, annual income, and birth country will be compared to that of the total eligible population, using data from the Longitudinal Integration Database for Health Insurance and Labour Market Studies (LISA) [43]. LISA is managed by Statistics Sweden (the agency of government statistics), which has a 100% coverage for all Swedish citizens aged > 16 years since 1990 and for all aged > 15 years since 2010. In Stockholm Region, the data from LISA is already integrated with the VAL database and used routinely. Additionally, we will assess case-finding rates (in both arms) defined as the proportion of participants where elevated levels of T2D and CVD risk factors are detected for the first time, e.g., the proportion of participants with prediabetes defined as a fasting blood glucose of 6.1–6.9 mmol/l and hypertension defined as blood pressure of ≥ 140/90 mmHg. Finally, semi-structured interviews will be conducted with one healthcare professional and potentially one manager from each participating PCC, with the aim of exploring barriers to and facilitators for implementation of the interventions. The interviews will be audio-recorded, transcribed verbatim, and analyzed using deductive content analysis [44]. The Consolidated Framework for Implementation Research will be used to guide the analysis [45]. Costs related to implementing and running HDI and OS will be analyzed using a bottoms-up, micro-costing approach. This includes staff training, time spent delivering the interventions, necessary materials, IT-infrastructure, etc.

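### Incident CVD is defined in words as ischemic heart disease and stroke but in codes as I00-I99; applied as written, the codes would count newly recorded hypertension as incident CVD

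*Protocol article*

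**What the plan says.** In the Protocol article, the opening sentence of Long-term health outcomes and resource use gives the outcome twice. In words, it covers "cases of incident T2D and CVD (ischemic heart disease and stroke) and deaths due to T2D and CVD". In codes, the cases are identified "using International Classification of Diseases, 10th revision (ICD-10) codes E11 for T2D and I00-I99 for CVD". Nothing else in the article narrows the code range or says which of the two governs.

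The same section lists the regional database VAL among the sources. VAL holds "data on diagnoses and healthcare utilization from inpatient, specialized outpatient, and primary care".

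Elsewhere the article keeps hypertension apart from CVD:

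- Health dialogue intervention (HDI) says that "detected risk factors for T2D and CVD (e.g., hypertension) will also be managed" under existing care programs, so hypertension is a risk factor there.
- Process and implementation outcomes makes it a case-finding outcome, namely "the proportion of participants where elevated levels of T2D and CVD risk factors are detected for the first time", with "hypertension defined as blood pressure of ≥ 140/90 mmHg" as an example.
- Objectives makes systolic blood pressure the surrogate for CVD incidence.

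**The concern.** I00-I99 is the full circulatory chapter of ICD-10. It contains the hypertensive diseases (I10-I15) and venous disease as well as ischemic heart disease and stroke. Hypertension is the most awkward of these here, because both arms look for it. If a hypertension diagnosis made at a primary care center after screening is coded and reaches VAL, it falls inside the coded endpoint, and a successful screen is recorded as a CVD event.

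Two things are at stake.

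- **The long-term comparison.** Incident CVD belongs to specific aim I. It feeds the Cox hazard ratios and the number needed to treat (Statistical analysis), and the 5- and 10-year incident-case and cost-consequence analyses (Health economic evaluation).
- **The check on the surrogate.** Under Unintended side effects, the article says that long-term follow-up will help show whether gains in surrogate markers carry over to the target outcomes. If the target includes hypertension, it is partly defined by the surrogate, and the check becomes partly circular.

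**Working it through.** The article states no event rate, event count or power for the long-term CVD outcome, so there is no figure of its own to reproduce. The calculation asks how far the coded endpoint can drift from the worded one.

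**Inputs from the article**
- A 5 mmHg reduction is taken to lower CVD risk by about 10% (Sample size). This is used as a true risk ratio of 0.90.
- Planned maximum of 3000 participants, so about 1500 per arm.
- Blood pressure is measured in both arms at baseline. In HDI, "The appointment will begin with an assessment of body weight, height, waist-to-hip ratio, and blood pressure"; the OS screening also includes it. It is measured again at 6 and 12 months (Biological risk factors).

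**Inputs assumed, because the article gives none**
- Risk of ischemic heart disease or stroke in OS: p = 5% (3-10% for the break-even). In HDI it is 0.90p, so 4.5%.
- Probability of a new hypertension code in OS: h = 10%, 20% or 30%. In HDI it is h + d.
- Hypertension codes are independent of ischemic heart disease and stroke.

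**Worded endpoint.** 1500 × 5% = 75 events in OS and 1500 × 4.5% = 67.5 in HDI; risk ratio 0.90.

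**Coded endpoint**
- OS risk = 1 − (1 − 0.05)(1 − h)
- HDI risk = 1 − (1 − 0.045)(1 − h − d)
- Share of OS events that are hypertension only = 1 − 0.05 / OS risk

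| h in OS | OS risk | Hypertension-only share | Risk ratio, d = 0 | d = +2 points | d = −3 points |
|---|---|---|---|---|---|
| 10% | 14.5% | 66% | 0.97 | 1.10 | 0.77 |
| 20% | 24.0% | 79% | 0.98 | 1.06 | 0.86 |
| 30% | 33.5% | 85% | 0.99 | 1.05 | 0.90 |

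Example, h = 10% and d = +2 points: HDI risk = 1 − 0.955 × 0.88 = 15.96%, and 15.96 / 14.5 = 1.10.

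On the hazard scale, approximated by ln(1 − HDI risk) / ln(1 − OS risk), the ranges are 0.97-0.99, 1.06-1.11 and 0.76-0.88 for the three values of d.

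**Break-even.** The excess of hypertension codes in HDI that cancels a true 10% reduction is d = (1 − h) × 0.1p / (1 − 0.9p). At p = 5% this runs from 0.7 × 0.005 / 0.955 = 0.37 points (h = 30%) to 0.9 × 0.005 / 0.955 = 0.47 points (h = 10%), or about 5.5 to 7 people per 1500. Over p = 3-10% it runs from 0.22 to 0.99 points, or about 3 to 15 people per 1500.

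**The case against.** The sentence can be read more kindly. I00-I99 may be only the range used to pull records from the registers, with the words in parentheses naming the endpoint. The same sentence also covers deaths, for which a whole-chapter range is less of a problem. The article's treatment of hypertension as a risk factor supports this reading. What stands is that counting hypertension as CVD is conditional on the codes governing. The contradiction itself remains: the article attaches that range to CVD without qualification and leaves two published definitions that can give different answers.

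A reader might infer three stronger claims. The article does not support them.

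- **That the long-term result would reverse.** Reversal needs more new hypertension codes in HDI than in OS, and the article gives no expected difference. Both arms are measured at baseline, 6 and 12 months. Equal detection dilutes the effect without reversing it, and fewer codes in HDI would leave the benefit about the same or exaggerate it. Equal detection is not assured either, because HDI invites enlisted patients by letter while OS recruits people who are attending anyway.
- **That every raised screening reading becomes an event.** The 140/90 mmHg threshold defines case finding. The article does not say that each such case receives a register diagnosis.
- **That people with known hypertension would drop out of the risk set, and unequally by arm.** No rule for prevalent cases is stated. The OS restriction concerns the reason for the appointment, so a patient with known hypertension who attends for something else stays eligible.

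It is also fair to say that this is not the trial's deciding analysis. With 1500 per arm, a hazard ratio of 0.90 and assumed risks of 3-10%, power on the worded endpoint is only about 7-14% before clustering. For example, at 5% there are 142.5 events, √(142.5/4) × 0.105 = 0.63, and Φ(0.63 − 1.96) ≈ 9%. That lowers the priority. It also means that a few miscounted diagnoses can move the estimate.

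**Conclusion.** The words and the codes for incident CVD are incompatible, and one of them has to change. If the codes are followed, the endpoint would probably consist mostly of hypertension: 66-85% of OS events under the assumptions above. With equal detection, a true ratio of 0.90 shrinks to 0.97-0.99. With unequal detection the bias can go either way, from 0.77 to 1.10 in the scenarios shown, and an excess of well under one percentage point in HDI is enough to cancel the benefit at a 5% baseline risk.

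The sizes rest on assumed rates and on independence. The contradiction rests only on the text. Systolic blood pressure, the other short-term outcomes and the 12-month economic results are not affected, so this is a correction that should be made before register outcomes are extracted. It is not a threat to the primary analysis.

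**What to change.** Make the incident-CVD codes match the stated definition: I20-I25 for ischemic heart disease and the stroke codes that the sponsor intends, with I10-I15 explicitly excluded. If the sponsor does want a broader outcome, the words should change instead and the role of hypertension should be stated.

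In the same edit:
- give the code range for CVD death separately;
- report new hypertension only as case finding;
- say how diagnoses recorded before or at the baseline screen are handled;
- use the same incident set in the Cox models, the number needed to treat and the 5- and 10-year economic analyses.

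The cost is a few lines in the protocol, the analysis plan and the registry entry, and fewer events than I00-I99 would yield. No data collection is lost, because the codes are applied at register extraction. Participant recruitment began in December 2023, so the 5-year outcomes were still years away when the article was published.

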### Process and implementation outcomes

Process and implementation outcomes will be assessed 6 months post intervention according to Proctor et al.’s taxonomy [41]. Adoption will be measured as the number of invited PCCs that agree to participate in the study. Healthcare professionals’ perceptions of how acceptable, appropriate, and feasible the interventions are to implement within the context of the PCCs will be assessed using the Acceptability of Intervention Measure, the Intervention Appropriateness Measure, and the Feasibility of Intervention Measure [42]. The measures consist of four items each and responses are reported on a 5-point Likert scale ranging from “completely disagree” to “completely agree.” Fidelity will be operationalized as adherence to the original intervention protocols and assessed using data from electronic medical records. For the HDI, we will report to what extent (proportion) all parameters of the screening have been assessed and whether the following health dialogue has been conducted, as based on documentation in the patients’ electronic medical records. For the OS, we will assess to what extent (proportion) all parameters of the screening have been assessed and to what extent that identification of an elevated risk factor has resulted in measures taken according to existing clinical practice guidelines. (For example, what proportion of participants who report daily smoking are given brief advice about smoking cessation and asked whether they want a referral to a qualified tobacco cessation advisor.) Penetration will be assessed in terms of the proportion (in both arms) of patients choosing to participate among those invited (attendance rate), and the reasons for declining participation among non-participants. We will also report (in both arms) the representativeness of participants as compared to the total eligible population based on socioeconomic characteristics. Participants data on sex, level of education, occupation, annual income, and birth country will be compared to that of the total eligible population, using data from the Longitudinal Integration Database for Health Insurance and Labour Market Studies (LISA) [43]. LISA is managed by Statistics Sweden (the agency of government statistics), which has a 100% coverage for all Swedish citizens aged > 16 years since 1990 and for all aged > 15 years since 2010. In Stockholm Region, the data from LISA is already integrated with the VAL database and used routinely. Additionally, we will assess case-finding rates (in both arms) defined as the proportion of participants where elevated levels of T2D and CVD risk factors are detected for the first time, e.g., the proportion of participants with prediabetes defined as a fasting blood glucose of 6.1–6.9 mmol/l and hypertension defined as blood pressure of ≥ 140/90 mmHg. Finally, semi-structured interviews will be conducted with one healthcare professional and potentially one manager from each participating PCC, with the aim of exploring barriers to and facilitators for implementation of the interventions. The interviews will be audio-recorded, transcribed verbatim, and analyzed using deductive content analysis [44]. The Consolidated Framework for Implementation Research will be used to guide the analysis [45]. Costs related to implementing and running HDI and OS will be analyzed using a bottoms-up, micro-costing approach. This includes staff training, time spent delivering the interventions, necessary materials, IT-infrastructure, etc.
